**Methods:**

Participants will be recruited through digital outreach, enrolled anonymously, and randomized into 6 groups to compare combinations of tips, nudges, and to-do lists. Engagement metrics (eg, clicks, completion rates, and session duration) and demographic data (eg, age and gender) will be collected. Statistical analyses will include a comparison between arms and interaction testing to evaluate the effectiveness of each intervention component. Ethical safeguards include institutional review board approval, informed consent, and strict data privacy standards.

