### Randomization

Participants will be randomly assigned to one of the following six arms, as presented in Figure 2:

Arm 1 (baseline control): directive tips only and no to-do checklist.Arm 2: directive tips + social proof tips and no to-do checklist.Arm 3: directive tips + social proof tips + present bias tips and no to-do checklist.Arm 4: directive tips + to-do checklist.Arm 5: directive tips + social proof tips + to-do checklist.Arm 6: gamification (progress bars) + to-do checklist.

Participants will be randomly assigned to one of the six experimental arms using computer-generated randomization in a 1:1:1:1:1:1 ratio. Randomization will be conducted at the point of user registration, ensuring equal probability of assignment to any condition. No stratification or blocking will be used, as randomization is expected to produce comparable groups given the planned sample size. Randomization will be logged automatically by the system to ensure reproducibility and allocation integrity.

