### Multiarm Trial Rationale

The six study arms were developed to explore the individual and combined effects of behavioral prompts grounded in behavioral economics, to identify which strategies most effectively enhance engagement in a digital resiliency program. Each arm includes a specific configuration of tips, checklists, or gamification elements intended to test distinct motivational mechanisms. This design enables comparative analysis across different engagement strategies while remaining operationally feasible. These components tested include (1) directive tips, grounded in the theory of implementation intentions, which provide straightforward, actionable guidance; (2) social proof tips, which leverage peer effects by referencing the behavior of others to encourage participation; (3) present bias tips, designed to counteract temporal discounting by emphasizing short-term benefits of engagement; (4) to-do checklists, which introduce structured goals and progress-tracking to increase adherence; and (5) gamification, which builds intrinsic motivation through visual indicators of advancement and progress feedback.

While a full factorial design could have explored all possible combinations of these interventions, the current 6-arm structure is a deliberate balance between conceptual rigor and practical feasibility. This structure enables comparative analysis across a diverse set of nudge combinations without creating an unmanageable number of trial arms. It was also informed by operational constraints and the need for meaningful data distribution across arms.

Our study design is also a foundational step toward developing a predictive analytics dataset. The behavioral engagement data collected through the six arms will be used to build baseline models that inform AI-driven personalization strategies. Future iterations of the course will be updated with tailored nudges based on user profiles, and new user data will be used to validate and refine the models. We chose the current design to generate sufficient diversity and volume in behavioral data to create a baseline for our long-term, adaptive research agenda.

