## Discussion

### Hypothesis

From our previous study, we anticipate higher engagement in arms that include the to-do checklist, particularly when combined with gamification (arm 6) or social proof tips (arm 5) (H1 and H2). Previously, these combinations demonstrated higher click-through and completion rates in earlier research. We expect similar trends in this trial, though results may vary based on population characteristics and platform context.

The study will also contribute to the development of AI models capable of predicting and optimizing user engagement, allowing for the customized delivery of to-do items and tips based on behavioral phenotypes (H2). These models will be trained using the behavioral data collected across study arms. Ultimately, this approach aims to enhance long-term adherence by tailoring interventions to individual patterns of use.

In our previous research on user engagement within the platform’s social network, we observed that engagement patterns followed power law distributions [88]. A follow-up study found that demographic and condition-specific characteristics did not predict social network engagement [89]. However, this study will help determine whether course engagement follows similar power law properties or if age and gender are predictive of engagement outcomes, particularly given the inclusion of session duration and behavioral phenotypes as new analytical factors (H3).

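### Arm 6 adds gamification and drops directive tips together, so the arm contrasts cannot give the separate effect of either, although the protocol claims both

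*Protocol article*

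**What the plan says.** The Randomization section of the protocol article lists six equally allocated arms. Three have no checklist: "Arm 1 (baseline control): directive tips only and no to-do checklist", "Arm 2: directive tips + social proof tips and no to-do checklist" and "Arm 3: directive tips + social proof tips + present bias tips and no to-do checklist". Three have one: "Arm 4: directive tips + to-do checklist", arm 5 (arm 4 plus social proof tips) and "Arm 6: gamification (progress bars) + to-do checklist". No tips of any type are listed for arm 6.

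The Multiarm Trial Rationale says the arms were built to "explore the individual and combined effects of behavioral prompts grounded in behavioral economics". Its numbered list of tested components includes directive tips (first) and gamification (fifth). It explains that a full factorial was rejected on grounds of feasibility, but does not say that any two listed components cannot be separated. The Methods paragraph of the Abstract promises "interaction testing to evaluate the effectiveness of each intervention component". The Hypothesis section expects more engagement in the checklist arms, "particularly when combined with gamification (arm 6) or social proof tips (arm 5".

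Two other sections bear on what arm 6 is. The Gamification section describes a progress bar and badges as implemented in this study, with no restriction to an arm. Table 3 (The Intervention) lists a gamified CBT course among the main components.

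**The concern.** Moving from arm 4 to arm 6 changes two things at once: gamification comes in and directive tips go out. If arm 6 does no better than arm 4, the progress bar may be useless, or it may help by as much as the lost tips cost. If arm 6 does better, the progress bar may help, or the tips may have put users off. The data cannot tell these cases apart.

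The primary outcome makes the comparison less even still. It is a click on a tip or a checklist item, and arm 6 as listed has only checklist items to click.

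The rationale intends these data to train personalization models. A model trained on them would inherit the ambiguity: the randomized arms cannot say whether to show progress bars or to withdraw tips.

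**Working it through.** The protocol gives no figure to reproduce here. The check is whether each component effect is estimable from the arm list.

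**Inputs** (Randomization section; 1 = present, 0 = not listed):

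| Arm | Directive (D) | Social proof (S) | Present bias (P) | Checklist (C) | Gamification (G) |
|---|---|---|---|---|---|
| 1 | 1 | 0 | 0 | 0 | 0 |
| 2 | 1 | 1 | 0 | 0 | 0 |
| 3 | 1 | 1 | 1 | 0 | 0 |
| 4 | 1 | 0 | 0 | 1 | 0 |
| 5 | 1 | 1 | 0 | 1 | 0 |
| 6 | 0 | 0 | 0 | 1 | 1 |

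**Model.** Take the case kindest to the design, with no interactions: arm mean = m + dD + sS + pP + cC + gG.

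**Contrasts.**
- Arm 2 − arm 1 = s, and arm 5 − arm 4 = s.
- Arm 3 − arm 2 = p.
- Arm 4 − arm 1 = c, and arm 5 − arm 2 = c.
- Arm 6 − arm 4 = (m + c + g) − (m + d + c) = g − d.

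**Estimability.** D + G = 1 in every row, so these two columns sum to the intercept column. The design matrix has six parameters and rank 5. The effects s, p and c are estimable. The effects d and g are not; only g − d is. More participants do not change this.

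**Two illustrative cases** (arbitrary units). With g = 0.3 and d = 0.3, arm 6 − arm 4 = 0. With g = 0 and d = −0.3, arm 6 − arm 4 = +0.3.

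**If gamification runs in all arms.** Then G = 1 in every row and arm 6 − arm 4 = −d. Gamification is still not estimable, and arm 6 becomes a test of removing tips.

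**Alternative arm sets.** If arm 6 were D + C + G, with G absent from arms 1 to 5, the rank stays 5, but g becomes estimable (arm 6 − arm 4) and d does not. A seventh arm, either C alone or D + C + G, gives rank 6 and all five effects.

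**Interactions.** Arms 1, 2, 4 and 5 form a 2 × 2 of social proof by checklist, estimated by (arm 5 − arm 4) − (arm 2 − arm 1). No other pair of components forms a 2 × 2: present bias never appears with the checklist or without social proof, and gamification never appears without the checklist or with tips. For a continuous outcome with 100 analysed per arm, 80% power and two-sided 0.05:
- interaction: (1.96 + 0.84) × √(4/100) = 0.56 SD;
- main effect in the same four arms: half of that, 0.28 SD;
- interaction with 85 per arm after the stated 15% attrition: 2.80 × √(4/85) = 0.61 SD.

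**Can the loss of tips be taken as negligible?** In the prior trial (Our Prior Work), mean completed components were 1.5 in control, 1.8 with tips and 2.11 with tips and checklist. The steps are 1.8 − 1.5 = 0.30 and 2.11 − 1.8 = 0.31, so the step with tips was about as large as the step with the checklist.

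**The case against.** The protocol openly chooses a non-factorial design and speaks of exploring effects, and every arm 6 contrast is a valid randomized comparison of packages. That stands, but the caveat does not tell the reader that two of the five named components are aliased. Nor does feasibility require it, since six arms can isolate gamification.

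A reader might infer that the gamification hypothesis cannot be tested at all. The document does not support that. The Hypothesis section ranks arms, and arms 4 to 6 against 1 to 3, or arm 6 against arm 4, test that ranking. What fails is crediting gamification with the result.

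A reader might also infer that directive tips go untested. The primary outcome covers clicks by type of tip, and Data Collection has each displayed tip logged. Click rates on directive tips can therefore be described within arms 1 to 5. This is not the randomized effect of having such tips against having none.

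Finally, a reader might take the prior trial's +0.30 as the size of the bias, so that an equal gamification gain would be exactly cancelled. It cannot bear that weight. It comes from a tip-of-the-day feature not described as directive, without a checklist, in another trial, on what is a secondary outcome here.

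**Conclusion.** The point holds as an over-claim built into the arm structure. On the arm list as written, gamification and directive tips are perfectly aliased, and arm 6 against arm 4 compares two packages. The Abstract and the Multiarm Trial Rationale claim more than the arms can deliver for these two components. The social proof, present bias and checklist contrasts stand, and so does the arm-level hypothesis.

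The size of the confounding is the directive-tip effect when a checklist is present, which the documents do not give. The prior trial shows only that it cannot be assumed negligible. The 0.56 SD interaction figure assumes a continuous outcome, whereas the primary outcome is a click.

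The conclusion rests on two readings. The first is that arm 6 has no tips because none is listed; the study flow figure was not available to confirm it. The second is that gamification is confined to arm 6, which the Gamification section and Table 3 put in doubt. If it runs in every arm, its effect is still not estimable.

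**What to change.** 1. Reconcile the Randomization section with the Gamification section and Table 3: state for each arm whether progress bars and badges are on, and whether arm 6 shows any tips.

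2. Before launch, choose one of the following:
   - Define arm 6 as directive tips + checklist + gamification, with gamification switched off in arms 1 to 5. Arm 6 against arm 4 then isolates gamification. The number of arms and participants is unchanged. The cost is a platform configuration change, which also touches arms 1 to 5 if gamification is now on there, and the loss of the tip-free arm.
   - Keep arm 6, call it a bundle, and state that no separate gamification effect will be claimed. This costs wording only, and it is the option left if enrolment has begun.

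3. In either case, remove directive tips from the components whose individual randomized effect is claimed, and present click rates by tip type as descriptive.

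4. In either case, limit interaction testing to social proof by checklist in arms 1, 2, 4 and 5, and reword the Abstract to match.

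If separate effects of both components are essential, a seventh arm (checklist alone, or directive tips + checklist + gamification) would provide them under additivity, with gamification off in arms 1 to 5. At the planned 100 per arm, that means another 100 participants.

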#### Sample Size Calculation for Regression Analysis

Regression analysis will be applied to assess the relationship between engagement and demographic factors (eg, age and gender). This will assist in the identification of predictors of engagement and potential subgroup effects [97]. These analyses are exploratory and may be underpowered. For linear regression, a common rule of thumb suggests 15-20 participants per predictor variable [98,99]. For logistic regression, a minimum of 10 outcome events per predictor variable is typically required [100].

A total of 600 participants will provide sufficient sample size power for multiple predictors while ensuring a balanced distribution across intervention arms. This sample size also accounts for expected variability in engagement behavior across arms and balances analytic rigor with the practical realities of digital recruitment.

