#### Sample Size for Repeated Measures

Since engagement data will be collected across multiple time points, generalized estimating equations will be used to account for within-subject correlations. The generalized estimating equation is well-suited for analyzing longitudinal behavioral data in real-world digital environments, allowing more accurate estimation of SEs and robust modeling of repeated engagement behavior. A within-group correlation of ρ=0.3 was assumed, based on prior studies of engagement in digital health. This estimate aligns with findings from longitudinal analysis in behavioral health studies that report moderate within-person correlation of repeated engagement measures [101,102]. A 15% attrition rate was factored into the final sample size, suggesting an adjusted recruitment target of 100 participants per arm to maintain statistical power.

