#### Sample Size Justification

To ensure the predictive model has sufficient training data, the study aims to recruit a minimum of 600 participants (100 per arm). This sample size balances feasibility with analytic rigor, ensuring adequate power to detect differences in engagement and to train AI-driven predictive models. Refer to Multimedia Appendix 1 for the study’s CONSORT-SPI (Consolidated Standards of Reporting Trials-Social and Psychological Interventions) checklist [103].

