## Results

This protocol was designed in January 2025. α and β testing of the intervention are scheduled to begin in July 2025, with a soft launch anticipated in August 2025. The experiment will remain active until the sample size requirements are met. Live monitoring and periodic data quality checks will be conducted throughout the study duration.

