### Strengths and Limitations

A strength of this experiment is that it will be conducted in an ad libitum environment. Unlike most digital health studies, it will not be conducted with a small population in a controlled environment. Further, members will not be aware of the experiment, which will limit participant bias and the Hawthorne effect.

Based on stratified randomization, which will balance demographic factors, the dataset generated will enable predictive analytics for adaptive engagement strategies. Other indication-specific data, such as results and qualifying criteria from the mental health screener [81], have the potential to enrich tailoring. These layers of data will help evolve the platform from static guidance toward real-time personalization.

A limitation of this experiment is that, especially due to the anonymity of members, we have no way of confirming user identity. Registrants may be displaced Ukrainians, individuals reviewing the program based on general interest, researchers, practitioners reviewing the platform for professional use, Evolution Health competitors, industry analysts, or other users who may not be engaging with the platform to help achieve wellness. Sensitivity analyses will be conducted to filter and exclude anomalous user engagement data.

Although engagement correlates with improved intervention outcomes, this study does not measure wellness improvements. Follow-up research will be required to establish clinical efficacy.

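### The Methods rule out stratification, yet the Discussion claims demographic balance from stratified randomization; as the Methods stand, that balance holds only in expectation

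*Protocol article*

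**What the plan says.** The allocation method is described in two places in the protocol article.

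- **Methods, Randomization.** Participants are allocated "using computer-generated randomization in a 1:1:1:1:1:1 ratio". On timing: "Randomization will be conducted at the point of user registration, ensuring equal probability of assignment to any condition". On restriction: "No stratification or blocking will be used, as randomization is expected to produce comparable groups given the planned sample size". This is simple (unrestricted) randomization.
- **Discussion, Strengths and Limitations.** "Based on stratified randomization, which will balance demographic factors, the dataset generated will enable predictive analytics for adaptive engagement strategies".

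Two other statements bear on balance. The section Sample Size Calculation for Regression Analysis says that 600 participants give sufficient power "while ensuring a balanced distribution across intervention arms". The Sample Size Justification says "the study aims to recruit a minimum of 600 participants (100 per arm".

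The Data Collection section names age and self-identified gender as the demographic items, recorded at registration or at secure sign-on. No section names a stratification factor or a block size.

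**The concern.** One section excludes stratification and gives a reason for doing so. The other credits stratification with a benefit. A reader of the Discussion would believe that demographic factors are balanced across arms by design, and that the dataset's value for predictive modelling rests on this. A reader of the Methods would know that no such control exists.

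The factors concerned are the ones the trial wants to study. Age and gender are the example predictors in the planned regression and appear in the third hypothesis. At stake is whether the article claims a design property that the trial lacks, and whether the analysis should carry strata. It is not whether the arm comparison is biased.

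**Working it through.** **1. The passages side by side**

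| | Randomization | Strengths and Limitations |
|---|---|---|
| Stratification | Excluded | Asserted |
| Blocking | Excluded | Not mentioned |
| Factors | None | Demographic factors, not specified |
| Source of comparability | Sample size | Stratification |

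No reading reconciles them. The Discussion sentence cannot be shorthand for a scheme defined elsewhere, because none is defined. Stratifying without blocks or another restriction would not help either: independent equal-probability allocation within strata is the same as simple randomization.

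**2. How much balance simple randomization gives**

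Inputs from the protocol: six arms, probability 1/6 each, 600 participants, so an expected arm size of 600/6 = 100. This agrees with the protocol's own figure.

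Assumptions, because the documents give no demographic distribution: a binary factor with prevalence p of 50%, 70% or 80%; a continuous factor measured in SD units; and thresholds of 10 percentage points and 0.2 SD for a visible imbalance.

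*Continuous factor, one named pair of arms.* The SD of the difference in means is √(1/100 + 1/100) = 0.141 SD. Then 0.2/0.141 = 1.414, and the two-sided normal tail beyond 1.414 is 0.157, or about 16%. For at least one of the 6 × 5/2 = 15 pairs, simulation gives about 72%.

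*Binary factor.* The SD of the difference between two arms is √(2p(1−p)/100). The probabilities below come from 20,000 simulated trials in which arm sizes also vary at random.

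| Assumed p | SD of difference, one pair | One named pair differs by more than 10 points | Mean spread, six arms | Spread exceeds 10 points |
|---|---|---|---|---|
| 50% | 7.1 points | 16% | 12.7 points | 72% |
| 70% | 6.5 points | 13% | 11.7 points | 64% |
| 80% | 5.7 points | 8% | 10.2 points | 49% |

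The spread is the highest arm minus the lowest, so it is the most extreme of the 15 pairwise differences. The named-pair column is the fairer guide to any single comparison.

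**3. Arm size**

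The SD of one arm's size is √(600 × 1/6 × 5/6) = 9.13, with a central 95% range of 82 to 118. The harmonic mean arm size averages 99.2, so unequal arms cost about (100 − 99.2)/100 = 0.8% in efficiency. Averaged over the simulated allocations, the power of the six-arm ANOVA at f = 0.1 is unchanged to the nearest percentage point.

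**The case against.** The strongest reply is that the operative method is not in doubt. The Randomization section gives ratio, timing, mechanism and a reason for omitting strata, and an implementer would follow it; the Discussion sentence is a stray clause. Simple randomization is also a legitimate choice. Chance imbalance is already allowed for in the standard errors and the type I error rate, and the Methods say only that comparable groups are expected, which is true. The size of the imbalance depends on an assumed prevalence, with 50% the least favourable case, and the six-arm spread takes the worst of 15 pairs. Estimating how age and gender relate to engagement does not require them to be balanced across arms. How the arm comparison is adjusted may be set out in a fuller document that is not shown.

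All of this stands, and it limits the point to a contradictory description and an unsupported claim of balance. It does not remove the contradiction.

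Two stronger readings are tempting. A reader might infer that the trial fails to deliver its 100 per arm. The documents do not support that. One hundred is the expected arm size under equal allocation, 600 is stated as a minimum, and on stopping the protocol says: "The experiment will remain active until the sample size requirements are met". No section promises exactly 100 in every arm at 600, and the efficiency cost of unequal arms is under 1%. A reader might also infer that the arm comparison is biased or invalid. It is not: unrestricted randomization is unbiased.

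**Conclusion.** The contradiction is established from the text alone. Under the Methods as written, the trial lacks the demographic balance by design that its Discussion lists as a strength. The wording in the regression sample-size section, which treats a balanced distribution as ensured, is also too strong for unrestricted allocation.

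The practical size is moderate. A spread of more than 10 percentage points across the six arms is expected in roughly half to three quarters of trials over the assumed prevalences (49% to 72%). A given pair of arms differs by more than 0.2 SD on a continuous factor in about 16%. These figures rest on about 100 participants per arm, the assumed prevalences and the chosen thresholds. They show that balance is not assured; they do not show bias, loss of validity or a material loss of power.

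**What to change.** Use one description of allocation throughout, settled before the first participant is randomized.

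- **If simple randomization stands:** delete the stratification and balance claim from Strengths and Limitations. In Sample Size Calculation for Regression Analysis, replace the assurance of balance with balance in expectation. Adjust the arm comparison for age and gender. The cost is two sentences of text and two covariates that are collected anyway.
- **If stratification is really intended:** rewrite the Randomization section to name the strata, with their categories, and to specify blocks within strata. Include the strata in the analysis. Because allocation happens at registration, the stratifying items must be available at that moment; Data Collection currently allows age and gender to come from either registration or secure sign-on. The cost is a change to the allocation routine before launch.

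Permuted blocks without strata are optional. They equalise arm size only and would not make the Discussion sentence true, so they do not replace either route.
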